#### IUDP 3 (Wuppertal)

In Wuppertal, two successive IUDPs have been implemented, with the first being launched in 2007 and later extended and renewed in 2014, reflecting a long-term, evolving strategy for urban development.

The first IUDP (2007) was based on an integrated approach aiming to combine structural upgrades, improved infrastructure, and social stabilisation. The overarching goal was to develop Elberfeld's northern district (a former independent city, incorporated into Wuppertal in 1929 and formalised under the 1975 local government reorganisation), including the Ölberg and Mirke areas, into an attractive, liveable, and sustainable district where urban quality, social inclusion, and community engagement go hand in hand.

Particular focus was placed on strengthening the high-quality residential areas in the northern district, especially the historicist buildings from the “Gründerzeit” period (late nineteenth century), and on creating new green spaces and playgrounds, addressing a previous lack of attractive recreational areas. The aim was to improve quality of life and prevent families from leaving by upgrading existing facilities. At the same time, a balanced land-use plan had to be developed, as the creation of additional green spaces competed with the high demand for parking. These efforts sought to enhance both quality of life in the neighbourhood and transport infrastructure for residents and local businesses. Social integration and educational support were equally important, as Elberfeld's northern district continues to be characterised by a high proportion of socially disadvantaged households despite positive developments. Expanding educational opportunities, promoting equal opportunities, and strengthening social cohesion were considered crucial for maintaining the district’s predominantly positive image over the long term.

Following the initial 2007 IUDP, the 2014 IUDP focused on maintaining or restoring the attractiveness of the districts as lively neighbourhoods with a mix of residential and commercial properties, while preventing further social and functional segregation. The programme focused on improving the living environment through new uses and repurposing of land and buildings, attractive façade design, developing concepts for commercial brownfield sites, refurbishing industrial monuments and backyards for new uses, and revitalising vacant shop premises. Throughout the framework of IUDP, issues such as gender mainstreaming, sustainability, demographic change, integration of people with a migration background, and inclusion of people with impairments and disabilities were consistently prioritised and embedded in both objectives and measures.

The central development goals of the IUDP included establishing Utopiastadt (literally “City of Utopia,” a community-driven urban development and cultural project) in the historic Mirke railway station as a laboratory and centre of excellence for urban, cultural, and social development, thereby reactivating the disused railway site as a business park, strengthening sustainable mobility, developing urban gardening as both an ecological and social strategy, and generally positioning the Mirke district as an intercultural hotspot. In addition, the programme aimed to develop the “Gründerzeit” buildings into an attractive residential area, promote zero-energy and energy self-sufficiency, and create model housing for older people with a migrant background.

### Outcomes

We will evaluate the IUDPs’ effects in relation to three entangled key dimensions: residents’ health, social equity, and ecological sustainability. To capture the complexity of change processes, we distinguish between different analytical levels, reflecting short- to long-term developments: “Outputs” refers to directly observable, short-term changes in the neighbourhood’s physical and social environment (e.g. new infrastructure, renovated public spaces), “Outcomes I” relates to early behavioural changes and modifications in local structural conditions, “Outcomes II” addresses medium-term effects on socio-ecological sustainability, such as increased participation or improved environmental quality, and “Impacts” describes long-term effects and more fundamental changes at the level of the broader societal system and overall context, such as strengthened resilience or reduced inequalities. To support this evaluation framework, we have developed a generic logic model applicable to all three IUDPs illustrating these levels and their interconnections (see Fig. 3).

**Fig. 3 Fig3:**
[figure not shown]
Logic model of the evaluation framework for Integrated Urban Development Plans

#### Residents’ health

Mainly, we will include subjective health status and different aspects of mental health to describe changes in the residents’ health. Health-related quality of life will be assessed using items from the German Federal Health Reporting surveys by the RKI, which include questions on general health status as well as physical limitations affecting daily activities. To complement this, we will measure the residents’ well-being, focusing on the more subjective and emotional aspects of their living conditions [20]. Additionally, the social network and integration will be evaluated by assessing the residents' social support [22], specifically the number of close people providing them with help and support.

#### Social equity

Regarding social equity, we will examine different aspects of environmental justice, namely distributional and procedural justice [37]. Distributional justice will be operationalised by analysing social disparities in exposure to environmental stressors as well as access to resources. Using survey data, we will compare living and housing conditions across different population groups, stratified by various socioeconomic factors such as income, education, migration experience, and employment status. Additionally, survey data will be used to analyse which social groups will be affected – positively or negatively – by potential changes resulting from the IUDP interventions.

To assess procedural justice, we will explore participants’ involvement in environmental and political decision-making. We will distinguish between three aspects: their knowledge of opportunities to participate in decision-making processes, their intention to engage – such as by signing a petition, attending an information event, or submitting a complaint to local authorities – and their actual past participation.

We will also use the Short Scale Measuring Perceived Social Participation to capture participants' perspectives on how they perceive their role within society [21].

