#### IUDP 1 (Bremen)

In Bremen Blumenthal, the IUDP was launched in 2023 with the aim of revitalising the historic district and creating healthier, more equitable living environments. The programme combines spatial, social, and physical environmental interventions to address long-standing challenges of structural inequality and urban neglect.

A significant contextual development is the construction of a new vocational training campus on the site of the former local wool factory, a large-scale industrial brownfield site. While formally not part of the IUDP, the campus is expected to attract thousands of students and professionals, offering new opportunities for education and employment as well as reshaping the district’s social and economic dynamics. The IUDP builds on this transformation by ensuring that the campus is well integrated into local life – for example through new pedestrian links to the district centre and measures that facilitate broad and inclusive access to its opportunities.

Complementary interventions within the IUDP focus on strengthening the social and cultural infrastructure of the historic centre. The former town hall will be renovated and repurposed as a multifunctional neighbourhood hub, hosting a library, community spaces, and social services to provide low-threshold access to resources and support. The surrounding market square, adjacent streets, and a large public green space will be redesigned to become more attractive, accessible, and inclusive areas for recreation and encounter, encouraging greater use by diverse groups of residents.

To counter widespread vacancy and housing neglect, the programme supports property owners with funding for renovations, energy-efficient upgrades, and heritage-sensitive restoration. In addition, the municipality has acquired several dilapidated housing units for renovation and reallocation as socially managed housing. These measures aim to ensure decent living conditions, reduce housing-related health risks, and prevent segregation and displacement.

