### Data analyses

To evaluate the effectiveness of IUDPs as complex interventions, the intervention areas will be compared with the control areas in regard to the aforementioned evaluation parameters. Regarding the IUDPs’ implementation, this includes an analysis of specific outputs, such as structural or socio-spatial changes in the neighbourhoods. In addition to the assessment of these outputs, we will focus on different outcome parameters in each city: in Bremen (I1, C1), these include Outcomes I and short-term Outcomes II; in Bochum (I2, C2), short- and long-term Outcomes II; and in Wuppertal (I3, C3), long-term Outcomes II and Impacts (Fig. 3).

Both bivariate and multivariate analyses will be conducted using established statistical procedures appropriate to the data structure. Quantitative data from the cross-sectional surveys at two time points, environmental data emerged from the different data collection formats, as well as secondary quantitative data collected at multiple time points, will be analysed using a difference-in-differences (DiD) approach [38]. Both absolute (difference-in-differences) and relative changes (ratio-of-ratios) will be assessed, and inequality effects will be examined through stratification by various social indicators [39]. From an intersectional perspective, social indicators will be selected based on the PROGRESS-Plus framework, as recommended by the Campbell and Cochrane Equity Methods Group [40]. The quantitative data analysis will be carried out using SAS (version 9.4 or higher) and R (version 4.5.1 or higher) [41].

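### Difference-in-differences within strata of current income or employment mixes an effect on a group with IUDP-driven movement between groups, and can mask or reverse a small true effect

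*Protocol article*

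**What the plan says.** The Social equity section of the protocol article operationalises distributional justice by comparing living and housing conditions in the survey across population groups, "stratified by various socioeconomic factors such as income, education, migration experience, and employment status". The sentence that follows makes an effect claim: "survey data will be used to analyse which social groups will be affected – positively or negatively – by potential changes resulting from the IUDP interventions".

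The Data analyses section applies DiD to the two surveys, on absolute and relative scales, and adds that "inequality effects will be examined through stratification by various social indicators". The final list is open: "social indicators will be selected based on the PROGRESS-Plus framework".

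Primary data collection methods describes two cross-sectional surveys, and Surveys of the residents places them in project years 1 and 3. The article describes neither a link between a respondent's two waves nor a question on earlier income or employment.

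On whether the plans can move these strata, IUDP 1 (Bremen) includes "measures that facilitate broad and inclusive access to its opportunities". The opportunities are those of a vocational campus, described as bringing education and employment but formally outside the IUDP. IUDP 3 (Wuppertal) lists "reactivating the disused railway site as a business park" among the goals of the 2014 plan, and says of the 2007 plan that "Expanding educational opportunities, promoting equal opportunities, and strengthening social cohesion were considered crucial".

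**The concern.** A stratum DiD reads as an effect on a group only if the intervention does not change who is in the group. Suppose an IUDP helps some unemployed residents into work, and they had better well-being than the other unemployed. Those still unemployed at wave 2 then have a lower mean than the unemployed at wave 1, although no individual got worse. The control area cancels movement common to both areas, not movement that the IUDP causes, and a larger sample does not remove the shift.

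Social equity is one of the study's three key dimensions. A programme that raised employment and harmed nobody could be reported as having done nothing for the unemployed, or as having slightly harmed them, with a widening gap.

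**Working it through.** The article gives no sample size, effect size or SD for the stratified analysis, so there is no stated figure to reproduce. The check is composition arithmetic.

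**Inputs**
- u, share in the low stratum at wave 1: 22.0%, the unemployment rate of Bremen Blumenthal in Table 1. Using it as a share of respondents is an assumption, since the rate may have another denominator.
- m, net movement out of the low stratum relative to control: assumed 1, 3 or 5 points. For scale, 3 points is the whole difference between Blumenthal and its control area in Table 1 (22.0% - 19.0%).
- a, how far movers' mean lies above the low-stratum mean: assumed 0.15, 0.25 or 0.5 SD.
- g, gap between strata: assumed 0.5 SD in the worked example.
- d, true effect, the same for everyone.

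**Formulas** (low-stratum mean at wave 1 set to 0)
- Low-stratum DiD = d - m·a/(u - m)
- High-stratum DiD = d - m·(g - a)/(1 - u + m)
- The low-stratum sign reverses when d < m·a/(u - m)

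**Nobody changes** (d = 0, m = 0.03, a = 0.25, g = 0.5)
- Low: -0.03 × 0.25/0.19 = -0.0395 SD
- High: -0.03 × 0.25/0.81 = -0.0093 SD
- Both strata appear to worsen, and the gap appears to widen by 0.0302 SD.

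**Everyone gains 0.03 SD**
- Low: 0.03 - 0.0395 = -0.0095 SD, so the sign is reversed
- High: 0.03 - 0.0093 = +0.0207 SD
- With strata that the IUDP does not move, both would show +0.03 SD.

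**True effect at which the low stratum shows zero (u = 22.0%)**

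| Net movement | a = 0.15 | a = 0.25 | a = 0.5 |
|---|---|---|---|
| 1 point | 0.007 | 0.012 | 0.024 |
| 3 points | 0.024 | 0.039 | 0.079 |
| 5 points | 0.044 | 0.074 | 0.147 |

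At 3 points, a true effect of 0.1 SD keeps its sign in every column. Reversing it needs the extreme corner: 5 of 22 points leaving on balance, with movers 0.5 SD above the stratum mean.

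**Sensitivity to u** (m = 0.03, a = 0.25). With Blumenthal's share on unemployment assistance (29.7%) the shift is 0.0075/0.267 = 0.028 SD. Smaller strata shift more for the same points moved: at Wuppertal Mirke's 10.8% it is 0.0075/0.078 = 0.096 SD, but 3 points would there be more than a quarter of the stratum.

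**Simulation** of 2,000,000 people, low stratum falling from 22% to 19%, gap 0.95 SD: low-stratum shift -0.046 SD at d = 0, -0.016 at d = 0.03, +0.004 at d = 0.05 and +0.054 at d = 0.1. This agrees with the formula in direction and order of size.

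**Against sampling error.** With an assumed 800 respondents per area and wave, the standard error of the low-stratum DiD is √(4/(800 × 0.22)) = 0.151 SD. A shift of 0.0395 SD is 0.0395/0.151 = 0.26 standard errors.

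**The case against.** The sentence that names the strata is a descriptive comparison of living and housing conditions. The effect sentence after it names no strata, and the indicators are still to be chosen. That status is current is inferred from the cross-sectional design, not written. This stands as a limit on how firmly the point can be put. But the two sentences use the same survey for the same purpose, the analysis section examines inequality effects by stratification, and on the design described wave-2 respondents can be classified only by wave-2 status. The open list is not itself the fault; it makes the correction easy.

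Area unemployment rates are already collected under Secondary data sources, and DiD is applied to secondary data. This also stands: a shift in area unemployment would be visible. It does not show movement between the survey's own strata, and nothing ties it to the reading of the stratified results.

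The gap between currently poor or unemployed residents and others, before and after, is a legitimate quantity for distributional justice. Agreed. It is a description of two current groups, not an effect on a group, and only the second reading is at issue.

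Four stronger readings are tempting but not supported:
- A reader might infer that the IUDPs set out to change residents' income. No section says so; income follows only through employment. In Bremen the main driver, the campus, is formally outside the IUDP. The Bochum description names no employment measure. The Wuppertal aims date from 2007 and 2014, with final measures funded in 2026, so movement between the two waves there is only possible.
- A reader might expect sign reversal generally. It needs a true effect that is small relative to net movement.
- A reader might expect a false shift of about two standard errors. That takes a fifth of the stratum leaving, and exactly those with the highest outcome values. At 22.0% a fifth is 4.4 points, more than the 3.0-point difference between Blumenthal and its control area.
- A reader might conclude that income and employment must be dropped, or that wave-1 status should define the strata. The first would discard core equity dimensions; the second presumes a linkage that the article does not describe.

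**Conclusion.** The point holds in a limited form. Two of the four named example strata, income and employment status, can be changed by the IUDP, clearly enough in Bremen and possibly in Wuppertal. IUDP-driven net movement between them stays in the stratum DiD. At 3 points from a 22% stratum the low stratum shifts by 0.024 to 0.079 SD for movers 0.15 to 0.5 SD above its mean, and by about 0.04 SD in the central case. That can mask or reverse a small true effect, not one of 0.1 SD. Movement, mover advantage and gap are all assumptions, because the article gives none of them. The shift is well below one standard error at the assumed sample size, so the risk is a biased equity statement rather than a spurious significant finding. Migration experience and, for most adults, completed education are not touched.

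**What to change.** In Social equity and Data analyses, state three things:
- Claims about the effect of an IUDP on a social group rest on characteristics it is unlikely to move between waves: age group, sex, migration experience and completed education.
- Results by current income and employment are kept, as a description of the gap between current groups at each wave.
- Beside them, the DiD in the share of respondents in each income and employment stratum is reported, next to the area unemployment rates already collected under Secondary data sources.

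This needs wording and a few extra tables from planned survey data, with no new collection. The cost is that income and employment results carry a weaker, descriptive interpretation.

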#### Ecological sustainability

To assess ecological sustainability, we will draw on multiple data sources. Information on urban green spaces relevant to quality of life and neighbourhood liveability will be collected through on-site inspections conducted by members of the study team. Complementary secondary data on the number and condition of trees within the study areas will be obtained from the respective local authorities. Additional secondary data from these authorities will include information on the proportion of sealed surfaces, which serves as an indicator of the area’s infiltration capacity.

With regard to sustainable mobility, we will assess the share of active mobility in the study areas based on participants’ self-reported usual modes of transport in the survey. Furthermore, we will provide an overview of the neighbourhood conditions that support or hinder active mobility.

### Participant timeline

Due to the mixed-methods approach, the study does not follow a single, linear participant timeline but instead comprises a complex structure of multiple data collections and assessments. These involve different participant groups and vary across study areas with respect to both timing and content. This design allows for the integration of complementary perspectives and the examination of change processes at different levels and stages, thereby providing a more comprehensive understanding of the health, social, and ecological impacts of the IUDPs.

### Data analyses

To evaluate the effectiveness of IUDPs as complex interventions, the intervention areas will be compared with the control areas in regard to the aforementioned evaluation parameters. Regarding the IUDPs’ implementation, this includes an analysis of specific outputs, such as structural or socio-spatial changes in the neighbourhoods. In addition to the assessment of these outputs, we will focus on different outcome parameters in each city: in Bremen (I1, C1), these include Outcomes I and short-term Outcomes II; in Bochum (I2, C2), short- and long-term Outcomes II; and in Wuppertal (I3, C3), long-term Outcomes II and Impacts (Fig. 3).

Both bivariate and multivariate analyses will be conducted using established statistical procedures appropriate to the data structure. Quantitative data from the cross-sectional surveys at two time points, environmental data emerged from the different data collection formats, as well as secondary quantitative data collected at multiple time points, will be analysed using a difference-in-differences (DiD) approach [38]. Both absolute (difference-in-differences) and relative changes (ratio-of-ratios) will be assessed, and inequality effects will be examined through stratification by various social indicators [39]. From an intersectional perspective, social indicators will be selected based on the PROGRESS-Plus framework, as recommended by the Campbell and Cochrane Equity Methods Group [40]. The quantitative data analysis will be carried out using SAS (version 9.4 or higher) and R (version 4.5.1 or higher) [41].

Qualitative data from semi-structured interviews and focus groups will be analysed using the method of qualitative content analysis as described by Kuckartz and Rädiker [42]. Unlike Mayring’s approach [43], this method allows not only category-based but also case-based analysis. For the present study, the content-structuring variant of content analysis will be applied [42]. The aim is to systematically structure the material by content. Data analysis will be conducted using MAXQDA software. To ensure quality of the coding process, the recommendations of Kuckartz and Rädiker [42] regarding intercoder agreement will be followed. Previous to the initial coding round, the main categories will be jointly defined by the study team and the interviews will then be independently coded by two team members using these main categories. During this process, the coders will record open questions and ideas for modifying the code tree. Afterwards, the two team members will compare their codes, agree on a consolidated version, and document this in the codebook. In addition, the identification of themes and subthemes will be discussed and agreed upon within the entire study team.

Accelerometer data will be processed using ActiLife software (ActiGraph, Pensacola, FL). Non-wear times will be defined based on the Troiano algorithm [28]. Acceleration measurements across three axes will be aggregated into vector magnitudes and expressed as average counts per minute. Minimum wear time is defined as 22 h per day on at least five consecutive days. Sleep scoring will be conducted according to algorithms developed by Cole and Kripke [29].

Access to study data will be restricted to members of the study team, and data storage will comply with applicable legal regulations.

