**Methods:**

We will compare three IUDP intervention areas with three control areas in the respective cities using a mixed-methods design. Quantitative and qualitative data will be collected to assess both process and outcome quality of the IUDPs. Primary data collections include resident surveys and focus groups, qualitative interviews with stakeholders, as well as environmental and infrastructural assessments, including air-quality measurements, site visits, and observations related to active mobility and urban green spaces. Secondary data on population structure, aggregated health indicators, and local implementation processes will be provided by the municipalities. Analyses will follow a difference-in-differences approach to identify changes attributable to IUDP implementation while accounting for similar developments in the control areas.

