## Methods

### Study setting

This study will evaluate the impact and process quality of IUDPs in three urban areas in Germany. The intervention areas are the districts of Blumenthal (I1) in the city of Bremen, federal state of Bremen in northern Germany, Wattenscheid-Mitte (I2) in Bochum and Mirke (I3) in Wuppertal, both cities located in the federal state of North Rhine-Westphalia in the western part of Germany. In each city, a further district will serve as control area in which no IUDP will be implemented. These control areas are Bremen Kirchhuchting (C1), Bochum Hofstede (C2) and Wuppertal Rott (C3). For the localisation of all six study areas within Germany and the respective cities, see Fig. 1.

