#### Surveys of the residents

We will conduct two surveys in the study areas, one in the first and the other in the third year of the project. The surveys will target residents aged 18 years and older living within the defined study areas. In Bremen and Wuppertal, all residents will receive a personal access code enabling them to complete the survey online. In Wattenscheid-Mitte, due to the substantially larger population, a random sample of residents will be invited to participate, with the number of invitations adjusted to achieve a sample size comparable to the other intervention areas. The survey will be implemented on LimeSurvey, an open-source online survey tool [19]. The survey will include a set of validated questionnaires: Warwick Edinburgh mental well-being scale [20], Short Scale Measuring Perceived Social Participation [21], Oslo-3-Items-Social-Support Scale [22], self-efficacy short scale [23], and Abbreviated Place Attachment Scale (APAS) [24]. We will also use items on general mental and physical health status from the German Federal Health Reporting surveys, provided by the Robert Koch Institute (RKI) [25]. Furthermore, we will collect information about the participants’ living and housing situation, their subjective assessment of their living environment concerning (1) traffic infrastructure, (2) impairments due to noise, air pollution, and other environmental threads, (3) the proximity and accessibility of public green spaces, as well as their perceived impact on and involvement in urban planning decisions affecting their living environment. We will provide translations of the questionnaire in the most common languages of the study areas.

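### With one IUDP area and one control area per city, the two-wave survey difference-in-differences cannot by itself attribute change to the IUDP

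*Protocol article*

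**What the plan says.** The abstract (Methods) announces the comparison: "We will compare three IUDP intervention areas with three control areas in the respective cities using a mixed-methods design". It gives the purpose of the DiD as "to identify changes attributable to IUDP implementation while accounting for similar developments in the control areas".

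The design behind this is one pair per city. Study setting: "In each city, a further district will serve as control area in which no IUDP will be implemented". Under Surveys of the residents, the article fixes the two waves: "We will conduct two surveys in the study areas, one in the first and the other in the third year of the project".

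Data analyses says that the cross-sectional surveys, the environmental data and the secondary data "will be analysed using a difference-in-differences (DiD) approach", and that "we will focus on different outcome parameters in each city": Outcomes I and short-term Outcomes II in Bremen, short- and long-term Outcomes II in Bochum, long-term Outcomes II and Impacts in Wuppertal. On method it says only this: "Both bivariate and multivariate analyses will be conducted using established statistical procedures appropriate to the data structure". No unit of inference or variance method is named.

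Three other places bear on the point.
- IUDP 1 (Bremen) describes a new vocational campus in Blumenthal, formally outside the IUDP, that is expected to bring thousands of students and professionals into the district.
- Secondary data sources plans municipal series reaching back ten years before each IUDP.
- The Discussion relies on matched control areas, monitoring of those areas and DiD.

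**The concern.** The IUDP varies only between areas. In a single city the DiD estimates the IUDP effect plus the difference between whatever else happened in the two districts between the waves. With one area per arm these two parts cannot be separated. The Blumenthal campus shows that this is a practical matter in this study. The safeguards in the Discussion deal with developments in the control areas. They do not deal with a non-IUDP change in the intervention area, or with the ordinary drift of two districts.

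Both survey waves also fall after each IUDP began. First measures date from the end of 2023 in Bremen, 2015 in Bochum and 2007 in Wuppertal, and the study was prospectively registered in May 2025. The survey therefore has no pre-IUDP trend against which to judge drift.

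Results are meant to inform municipalities and policymakers about effectiveness. A district fluctuation could be read as proof that an IUDP worked or failed, and a larger survey would make the misreading look more certain.

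**Working it through.** The article states no sample size, power or error rate, so there is no figure to reproduce. What follows is illustration under stated assumptions, apart from the area-level limits in step 3.

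**1. Respondent-level interval, equal cell sizes.** Assumptions: outcome SD 1; n respondents in each of the four area-by-wave cells; an independent area-by-wave shock taking a share ρ of the variance; two-sided 5% test.
- Respondent-level SE of the DiD = √(4/n). For n = 1,000 this is 0.063 SD.
- Ratio of true to respondent-level SE = √(((1−ρ)/n + ρ)·n) = √(1 − ρ + nρ).
- Rejection rate with no IUDP effect = 2·(1 − Φ(1.96/ratio)).

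| n per cell | ρ = 0 | ρ = 0.1% | ρ = 0.5% | ρ = 1% |
|---|---|---|---|---|
| 500: SE ratio | 1.00 | 1.22 | 1.87 | 2.45 |
| 500: rejection | 5% | 11% | 29% | 42% |
| 1,000: SE ratio | 1.00 | 1.41 | 2.45 | 3.32 |
| 1,000: rejection | 5% | 17% | 42% | 55% |

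Rejection rises with n because sampling error shrinks and area error does not. The true SE cannot fall below 2√ρ, which is 0.14 SD at ρ = 0.5%, however many people respond.

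**2. The same check with the article's populations.** Adults from Table 1: Blumenthal 10,706 × (1 − 0.236) = 8,179; Kirchhuchting 9,356 × (1 − 0.225) = 7,251. Response rates and the shock SD τ (so ρ = τ²) are assumed. Respondent-level variance v = 2/n_I + 2/n_C; true variance v + 4τ².

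| Response | n_I / n_C | √v | τ = 0.03 | τ = 0.05 | τ = 0.10 |
|---|---|---|---|---|---|
| 5% | 409 / 363 | 0.102 | 9% | 16% | 37% |
| 10% | 818 / 725 | 0.072 | 13% | 25% | 51% |
| 20% | 1,636 / 1,450 | 0.051 | 20% | 37% | 63% |

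Worked cell (10%, τ = 0.05): v = 2/818 + 2/725 = 0.0052; true SE = √(0.0052 + 0.0100) = 0.123; 1.96 × 0.072/0.123 = 1.15; rejection 25%. Wuppertal is almost identical.

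**3. What area-level inference could give.** These limits need no variance assumption.
- The smallest two-sided sign-flip p with k pairs is 2/2^k: 1.0 for one pair, 0.50 for two, 0.25 for three.
- A t interval is undefined with one pair. Its multiplier is 12.7 with two and 4.30 with three.

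**4. What other districts could add for municipal indicators.** The smallest placebo-rank p with k comparison districts is 1/(k+1): 0.50 with one (the present design), 0.167 with 5, 0.10 with 9, 0.05 with 19. The documents do not give the number of districts. A crude indication is the rest of the city divided by the mean size of its two study areas:
- Bremen: 566,209 / 10,031 ≈ 56.
- Bochum: 341,554 / 16,825 ≈ 20, or about 15 if the areas are as large as the intervention area.
- Wuppertal: 339,439 / 9,380.5 ≈ 36.

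Restricting to similarly disadvantaged IUDP-free districts would lower all of these.

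**The case against.** The strongest reply is that the article never says respondent-level intervals or significance tests will be used. It promises procedures suited to the data structure, and the choice of variance is normal content for an analysis plan that is not shown. That stands: a reader might infer that false-positive IUDP effects will be reported, but the documents do not support it. What an analysis plan cannot do is estimate area-level variance from two areas and two survey waves. The mismatch between the design and the attribution aim is fixed in the article itself.

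A reader might also infer that the city-specific focus throws away the study's replication. The documents do not support this either. The areas were chosen because their IUDPs are at different stages, so the three pairs do not replicate one effect. The outcome levels overlap between cities (short-term Outcomes II in Bremen and Bochum, long-term in Bochum and Wuppertal), outputs are assessed in every city, and one survey is described for all areas. A focus does not exclude other outcomes. Even full pooling of three pairs could not go below p = 0.25. The one-against-one comparison comes from having one pair per city, not from the outcome focus.

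Nor is it right that drift can never be measured. The ten-year series under Secondary data sources can show it for municipal indicators. Conversely, other districts do not rescue the survey: survey scales, accelerometry (I1 and C1 only) and the project's own air measurements are not planned outside the study areas.

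**Conclusion.** The point holds in this form: for the two-wave survey, a city's IUDP effect is fully confounded with any other change specific to one of its two districts, and DiD against a single control area cannot by itself deliver attribution. This conclusion follows from the design and needs no numerical assumption.

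The error rates do need assumptions. The 11% to 55% range rests on area-by-wave variance shares of 0.1% to 1%, 500 to 1,000 respondents per cell, and intervals built from respondents. None of these is in the documents, and with zero area variance the rate is the nominal 5%. The figures show that a small area-level share is enough to matter; they do not predict what the study will report.

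**What to change.** 1. In the abstract and in Data analyses, state that DiDs from the survey, accelerometry and other primary data are city-specific, conditional on the chosen areas, and do not alone support attribution. If respondent-level intervals are shown, say that they cover sampling error only.
2. For secondary indicators, use the planned pre-IUDP series to show how far each pair diverged without an IUDP. Confirm that the series covers the control areas too, since the sentence on the ten-year period stands in the paragraph on intervention areas. For Wuppertal, take the window before 2007: ten years before the 2014 renewal would include the preceding IUDP. Where a municipality holds the same indicator for other IUDP-free districts, rank the IUDP area's DiD among those placebo districts.
3. Report the common survey outcomes for all three pairs side by side as description, read in light of the different IUDP stages and not as a replication test.

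Cost: more modest claims, some added analysis, and a wider data request limited to indicators available at district level. That request may not be small. Wuppertal would need series from about 1997, and Table 1 already shows missing ratios and a different age band for Bochum. The number of usable districts is not in the documents. Items 1 and 3 need no new data.
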